## Participants

Subjects will be recruited in hospital settings in at least 15 healthcare facilities in the US (including Puerto Rico) and Turkey where RBC transfusions are routinely performed for acute and chronic anemia. Site selection criteria for the chronic anemia cohort, including RCE, are dependent on investigators’ access to potential subjects. Clinical research staff at all participating sites will prospectively review patient admissions records, surgical calendars and other hospital records to identify potential subjects. A list of study sites is available on clinicaltrials.gov.

The target population includes patients aged ≥ 4 years who require or are expected to require an RBC transfusion or RCE. Informed consent will be obtained by the site investigators or by authorized and trained study staff using an approved informed consent form (ICF) developed in compliance with ICH GCP, regional regulatory requirements, and applicable laws. Investigators will obtain (and retain in the study file) written informed consent from each patient or the patient's legally acceptable representative before any trial-specific activity is performed. The ICF must be prospectively approved by both the Sponsor and each study site’s IRB or institutional ethics committee (IEC) before use and after any revisions to the protocol. Female subjects of child-bearing potential must have a negative pregnancy test within 30 days of randomization and agree to use at least one method of birth control during the study with a demonstrated low failure rate (< 1%). Patients will be excluded prior to randomization if they meet any of the criteria shown in Table 3. Exclusion criteria apply at the time of randomization. There are no specific exclusion criteria after randomization, with the exception of treatment-emergent antibodies to INTERCEPT RBCs, which would trigger a patient’s withdrawal from the active transfusion component of the trial.

**Table 3 Tab3:** Exclusion criteria

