### Screening/randomization (day −30 to day 0 pre-surgery)

Patients will be approached, consented (or assented, if appropriate), screened for eligibility, and randomized into one of the study arms (28 day acute; 28-day + 6-month extension) by investigators at each site. Subjects < 18 years of age will require subject assent and parental consent. For subjects eligible for enrollment into the six-month extension period, consent/assent for the extension period will be obtained at initial enrollment. Patients who consent to the study will be assigned a study ID number and undergo screening procedures described in Tables 1 and 2.

Screening data collection and procedures will include: demographics (age, sex), vital signs, height, weight, indication for anticipated transfusion, type of scheduled surgery (if applicable), medical and surgical history, transfusion history, physical examination, comorbid conditions, concomitant medications, hematology panel, blood type and Rhesus factor, indirect antibody test (IAT), blood chemistry panel, coagulation panel, direct antibody test (DAT), immune reactivity to amustaline/GSH RBCs, and pregnancy test (when applicable; performed within 30 days of randomization). The assays included in each of the panels referenced above are listed in the footnotes of Tables 1 and 2.

If results from the Screening assessments listed in Table 1 are available in the medical record within 30 days prior to randomization, those data may serve as the screening data and the assessments do not need to be repeated unless the subject has a non-study RBC transfusion in the 30-day period. If a non-study RBC transfusion occurs after a subject is determined to be eligible, but prior to randomization, the subject may be randomized and screening assessments will be repeated prior to the first study transfusion.

For SCD patients on a regular RCE program the pre- and post- RCE total Hb, HbA, HbS and HbF concentrations should be recorded from the medical record, if available, for up to 6 months prior to the first study transfusion (Table 2).

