### Randomization

An Interactive Web Response System (IWRS) will be used for electronic randomization of eligible patients. At the end of screening and prior to the first study RBC transfusion, the patient’s eligibility status will be entered into the study EDC system. If eligible, the patient will be randomized to receive either amustaline/GSH or conventional RBCs in a 1:1 ratio. Randomization will be stratified by site, baseline bleeding status (indication for RBC transfusion due to active bleeding or for anemia without active bleeding), patients’ participation in the optional extension period, and patients’ need for RCE (Fig. 2). Active bleeding will be defined as Grade 3 or 4 bleeding of the expanded WHO bleeding scale. Anticipated surgical bleeding and planned blood loss/replacement through RCE at baseline should be included as active bleeding (Grade ≥ 3) by definition.

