## Outcomes

### Primary and secondary endpoints

The primary safety endpoints include the proportion of subjects with any TEAEs possibly, probably or definitely related to a study RBC through 28-days after the last study transfusion, and the proportion of subjects with treatment-emergent antibodies with confirmed specificity to PR-RBCs. The primary efficacy endpoint is the adjusted Hb increment averaged over multiple transfusions for all non-bleeding subjects at baseline, defined as the difference between pre- and 15-min-24 h post-transfusion Hb values divided by the total Hb content transfused during each transfusion episode.

Secondary efficacy and safety endpoints will include:Adjusted Hb consumption defined as total Hb mass transfused (g) divided by body weight (kg) and the duration of the study transfusion period (days) in patients without active bleeding at baseline.HbA clearance in SCD patients undergoing regular RCE.All TEAEs for 28 days after last study transfusion.Transfusion reactions related to study RBCs (as defined by the CDC National Healthcare Safety Network [NHSN] Hemovigilance Module protocol), for 28 days after the last study transfusion.Treatment-emergent immunization to RBC alloantigens.All-cause mortality through 28 days after the last study transfusion.

Secondary Safety Endpoints (for SCD patients undergoing RCE):Proportion of subjects with adverse events of special interest (AESI) through 28 days after the last study transfusion.S-300 and GSH plasma levels before and 15 min to 4 h after RCE.

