### Statistical methods

Only patients in the mITT analysis set will be included in the efficacy analysis. Non-study RBCs received during the study transfusion period will be included to calculate the total Hb content transfused for the two efficacy endpoints in the mITT analysis set. Patients receiving non-study RBC transfusions as their first study transfusion will be excluded from the Per Protocol (PP) analysis set and only those transfusions that occur before a non-study transfusion will be analyzed. Data from the initial 28-day period and the optional 6-month extension period will be summarized together and separately.

Treatment difference in non-bleeding mITT patients will be assessed using a non-inferiority test with a pre-specified non-inferiority margin (15% of the Control mean value), stratified by site. An analysis of variance (ANOVA) model will be used to estimate and test the treatment effects while controlling for the clinical site. Non-inferiority will be declared if the lower bound of a 2-sided 95% confidence interval for the mean treatment difference (Test—0.85 × Control) is greater than or equal to zero.

For the primary efficacy endpoint, the adjusted Hb increment will be averaged over one or more transfusion episodes. An episode-specific Hb increment will be calculated by subtracting the Hb value before each transfusion episode from the Hb value taken 15-min-to-24-h after each transfusion episode. The relatively long post-transfusion assessment period is justified by prior findings that post-transfusion hemoglobin increments are not meaningfully impacted by the timing of the samples collected between 15 min and 24-h post-transfusion [14, 15]. Increments will be adjusted by the Hb content transfused in each given episode (which may contain multiple RBC components). The Hb content of each transfused RBC component will be calculated using the Hb concentration and post-sample weight of the RBC component (both measured at the blood center), and the percentage of the unit transfused (assessed at the hospital). The Hb mass of each transfusion episode is the sum of the Hb content for all RBC components transfused.

The Hb content transfused (g) for a study RBC component will be calculated as:$$post sampling weight \left(g\right)\div 1.06 \left(\frac{g}{mL}\right)\times percent of unit transfused \times hemoglobin concentration (g/mL)\div 100$$

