Non-study RBCs received during the study transfusion period will be included in the calculation of Hb content transfused. For each non-study RBC component received, the Hb content will be imputed using the average Hb content per study RBC component from the Control group within each clinical site.

The treatment difference in the adjusted Hb increment will also be summarized descriptively (with a 95% confidence interval) as exploratory analyses for the following mITT subgroups:Repeatedly transfused non-bleeding patients (defined as non-bleeding patients who receive at least 3 study RBC episodes).Subgroup by clinical site, age group (< 18, 18–64, and ≥ 65 years old), sex, and race (e.g., white vs. other races), as appropriate.

For SCD patients enrolled in the 6-month extension for three RCE procedures, HbA clearance will be estimated from the area under the curve (AUC) calculated by the trapezoidal rule based on measurements from samples collected within 4-h of each RCE, on Day 14 (± 7-days) and prior to the next scheduled RCE. Values will be adjusted by the duration in days used to calculate the AUC (i.e., between the 15 min-to-4-h post-transfusion sample and pre-transfusion sample of the next transfusion) and averaged over all study RCE procedures for each patient.

For the secondary efficacy endpoint of Hb consumption, the analysis will be conducted only in non-bleeding mITT patients who participate in both of the initial 28-day and 6-month extension periods and will utilize integrated data from both periods. Treatment differences in non-bleeding mITT patients will be assessed using the same non-inferiority test methods described above for the primary endpoint analysis. Interaction terms between the treatment and covariates will be explored, as necessary. For the adjusted Hb consumption analysis, the upper bound of a two-sided 95% confidence interval for the treatment difference (Test – 1.15 × Control) less than or equal to zero will result in the rejection of inferiority null hypothesis and the conclusion of non-inferiority.

Adjusted Hb consumption will be calculated as total Hb mass transfused in grams divided by body weight in kg at baseline and duration of the study transfusion period in days (g/kg/day). The total Hb mass transfused is the sum of the Hb content for all study and non-study RBC components transfused during the study transfusion period (i.e., 28 days or 28-day + 6-months, unless subjects prematurely discontinue the study).

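### The primary Hb increment per gram depends on body size, yet the ANOVA adjusts for site alone and leaves out the baseline weight already collected

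*Protocol article*

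**What the plan says.** The Primary and secondary endpoints section gives the adjusted Hb increment as "defined as the difference between pre- and 15-min-24 h post-transfusion Hb values divided by the total Hb content transfused during each transfusion episode", averaged over episodes. Nothing in it refers to body size.

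The Statistical methods section states the model: "An analysis of variance (ANOVA) model will be used to estimate and test the treatment effects while controlling for the clinical site". No other term is named for the primary analysis. Non-inferiority is declared when the lower 95% bound for Test minus 0.85 × Control is at least zero.

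On the population, the Participants section says: "The target population includes patients aged ≥ 4 years who require or are expected to require an RBC transfusion or RCE". Weight is available: the screening section lists "demographics (age, sex), vital signs, height, weight, indication for anticipated transfusion", and Table 1 has a weight row. It is used for the secondary endpoint: "Adjusted Hb consumption will be calculated as total Hb mass transfused in grams divided by body weight in kg at baseline".

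Weight and age play no part in allocation. The Randomization section begins "Randomization will be stratified by site, baseline bleeding status" and goes on to extension participation and need for RCE. For the primary endpoint, age and sex appear only among the descriptive exploratory analyses: "Subgroup by clinical site, age group (< 18, 18–64, and ≥ 65 years old), sex, and race (e.g., white vs. other races), as appropriate".

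**The concern.** Dividing by grams transfused removes the dose but not the volume into which the dose is diluted. A gram of haemoglobin given to a small child raises concentration several times more than a gram given to a large adult, whichever product is used. That spread is predictable from a variable already in the database, yet the named model counts it as noise.

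Two things are at stake. First, residual variance is larger than it need be in a non-inferiority test planned at 80% power. A few children with values several times the adult level could also push the CV above the planned 50%. Second, a chance imbalance in weight between arms passes straight into the estimated treatment difference, because weight is neither stratified nor adjusted for. Enrolment has closed, so precision can no longer be gained from more subjects.

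**Working it through.** **Inputs from the documents** (Abstract; Sample size; Statistical methods): margin 15% of the Control mean, no true difference, CV 50%, two-sided alpha 0.05, 1:1 allocation, 352 evaluable for 80% power and 468 for 90%. The Sample size section prints approximately 174 per group; 352/2 = 176, as in the Abstract, and 176 is used here.

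**Inputs assumed**, because the documents give none: blood volume 70 mL/kg (0.7 dL/kg), the weight distribution, and the share of children.

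**Step 1: the plan's own figure.** In units of the Control mean, n per arm = 2 × [(1.960 + 0.842) × 0.50/0.15]² = 174.4, so 175 per arm and 350 in total, against 352 stated. For 90%, 2 × [(1.960 + 1.282) × 0.50/0.15]² = 233.5, so 234 per arm and 468 in total, as stated. The sample size is correct for an unadjusted CV of 50%.

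**Step 2: the decision rule as written.** For Test − 0.85 × Control the variance factor is 1 + 0.85² = 1.7225 instead of 2. Power at 176 per arm is Φ(0.15/[0.50 × √(1.7225/176)] − 1.960) = Φ(1.07) = 86%. This is the baseline for the simulations below.

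**Step 3: effect of body size.** One gram gives 1/(0.7 × weight) g/dL: 0.089 at 16 kg, 0.071 at 20 kg, 0.036 at 40 kg, 0.020 at 70 kg, 0.018 at 80 kg and 0.014 at 100 kg. The range is four-fold from 20 to 80 kg and about six-fold from 16 to 100 kg.

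**Step 4: share of variance.** If the endpoint is a constant over weight, times independent noise, the share due to 1/weight is CV(1/weight)² / 0.50². For lognormal weights with log-SD s, CV(1/weight)² = exp(s²) − 1.

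- s = 0.15: 0.0228/0.25 = 9%
- s = 0.22: 0.0496/0.25 = 20%
- s = 0.25: 0.0645/0.25 = 26%

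With s = 0.22, adult median 75 kg and children uniform on 16–60 kg, CV(1/weight) is 0.296 with 2% children (share 35%) and 0.370 with 5% children (share 55%).

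**Step 5: what adjustment buys.** Residual CV = 50% × √(1 − R²), put into the Step 1 formula:

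| R² (assumed) | Residual CV | Total N for 80% | Power at 176 per arm |
|---|---|---|---|
| 0 | 50.0% | 350 | 80.4% |
| 0.1 | 47.4% | 314 | 84.3% |
| 0.2 | 44.7% | 280 | 88.2% |
| 0.3 | 41.8% | 246 | 92.0% |
| 0.5 | 35.4% | 176 | 97.8% |

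Simulation of the stated rule (176 per arm, total CV 50%, Step 4 weights, no site effect, 4,000 runs), power without and with 1/weight:

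- no children: 86% v 92%
- 2% children: 86% v 96%
- 5% children: 86% v 99%

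At a true ratio of 0.85, rejection was 2.2% to 3.1% with or without adjustment.

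**Step 6: does site already do the job?** With 15 site terms in both models (number assumed, Step 4 weights, 1,500 runs):

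- no children: 86% v 93%
- 3% children spread over sites: 85% v 97%
- 3% children all at one site: 88% v 98%

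**Step 7: if the CV is worse than planned.** At a total CV of 60%, still with site terms, power is 70% v 76% with no children and 73% v 90% with 5% children spread over sites. A run without site terms and under other weight assumptions gave 70% v 95% for 5% children, so this gain is sensitive to the inputs.

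**Step 8: chance imbalance.** The SD of the arm difference in mean 1/weight, relative to its mean, is CV(1/weight) × √(2/176). With adults only this is 0.222 × 0.107 = 2.4%; with 5% children it is 0.370 × 0.107 = 3.9%. Unadjusted, a shift of that size enters the treatment difference directly, against a 15% margin.

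**The case against.** The best case for the plan is that nothing in it is invalid. Under 1:1 randomisation the site-adjusted ANOVA controls type I error, and its confidence interval already allows for chance imbalance in weight. The 50% CV is for the endpoint as defined, so it may already include size variation; on that footing no promised power is lost, and the stated rule gives about 86% at 352. All of this stands, and it rules out any claim of bias or of a wrong sample size.

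It is also fair that the larger gains depend on weights and shares of children that the documents do not give. Eligibility from age 4 does not show that children form 3% to 5% of the non-bleeding set.

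Site adjustment could absorb much of the effect if children cluster. Across different assumptions, with 3% of subjects being children at one site, the planned model had 88% to 96% power, against 98% to 99% with 1/weight. Clustering therefore shrinks the gain without removing it, and the adults-only gain does not depend on children at all.

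Scaling the secondary endpoint by weight is not in itself an inconsistency, since consumption is a different quantity.

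Finally, the SAP was not available for this check and might carry further covariates. But the article names the primary model and its one control variable, so this is a stated choice. The article's remark on interactions with covariates sits in the Hb consumption paragraph and adds no weight term to the primary model.

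**Conclusion.** The concern holds as a loss of precision, not as bias. The endpoint varies inversely with body size, the eligible range starts at 4 years, weight is on file, and the named primary model omits it. At 176 per arm and a total CV of 50%, adding 1/weight would remove about 9% to 26% of the error variance with adults only, and roughly a third to a half with 2% to 5% children. Power under the stated rule would rise from about 86% to 92% with a mid-range adult spread, and to 96% to 99% with children. Type I error is unaffected. These sizes rest on assumed weights, an assumed 70 mL/kg and an assumed share of children; the direction does not depend on the particular values. The change should be made, but the planned test would still be valid without it.

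**What to change.** Replace the site-only ANOVA by an ANCOVA with treatment, site and 1/baseline weight (or 1/estimated blood volume), prespecified as the primary model. Apply the Test − 0.85 × Control contrast to the adjusted means. Leave the endpoint, margin and sample size unchanged, and keep the site-only model as a sensitivity analysis. If the SAP already contains such a term, bring the article's description into line with it.

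The cost is a change of wording in the SAP and the matching protocol text. No new data are needed. Timing matters: the Discussion says the study is still blinded, and the Participants section expects last assessments in the third quarter of 2026. The covariate can be fixed credibly now; after unblinding the same adjustment would be post hoc.

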**Study Assessments**	**Screening**	**Transfusion Support Periods** • **Day 1 through Day 28 *****and*** • **28-Day plus 6-month extension (or death-up to 10 transfusion episodes)**		**Follow-Up Visit Day 28* (28 ± 7 days) after last study transfusion episode**	**End of Study-Day 75 of** ** Follow-Up (75 ± 15 days) after last study transfusion**
		**Before each transfusion episode**	**15 min—24 h. after each transfusion episode**		
Informed Consent (assent, if appropriate)	X^1^				
Medical, surgical, prior transfusion and medication history	X^1^				
Physical exam, including height	X^1^				
Weight	X^1^				
Demographics	X^1^				
ABO Blood type and Rh^3^	X^1^	X^3^			
Indirect Antiglobulin Test^3^	X^1^	X^3^		X	
DAT^8^	X^1^			X	X
Immune reactivity to amustaline/GSH RBCs (amustaline/GSH RBC antibody testing)	X^1^	X^7^		X	X
Pregnancy test (if applicable)^3^	X				
Indication for RBC transfusion	X^1^				
Hematology panel^9^	X^1^	X		X	
Hemoglobin measurement			X^2^		
Blood chemistry panel^10^	X^1^	X		X	
Coagulation panel^11^	X^1^			X	
Vital signs	X^1^	X	X	X	
RBC transfusion data (study or non-study)	X^1^	X		X^5^	
Concomitant medications	X^1^	X^4^		X	
Other blood components transfused		X		X	
Procedure details (as applicable, e.g., surgery)		X			
Adverse events and transfusion reactions		X	X	X^13^	
SAEs		X	X	X^13^	
Surveillance calls ^12^		X		X	
Documentation of vital status		X		X	X
Assess proportion of each RBC component transfused (e.g., 25%, 50%, 75% or 100%) For pediatric patients, the volume of the intended transfusion should be recorded			X		
Assessment of bleeding status^6^	X	X			

‡ Randomization of eligible subjects may occur any time up to 30 days prior to first study transfusion

* Day 1 of the follow-up period is the first day after the last study transfusion

^1^If results from the Screening assessments listed are available in the medical record within 30 days prior to randomization, those data may serve as the screening data and the assessments do not need to be repeated unless the subject has an RBC transfusion in the 30-day period. If an RBC transfusion occurs after determined eligibility but prior to randomization, the subject may be randomized, and those Screening assessments listed above should be repeated prior to the first study transfusion

^2^Hb measurement at 15 min to 24 h post transfusion episode (before the next RBC transfusion episode)

^3^Routine standard of care test order per local hospital SOPs

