^4^Medications administered during anesthesia for surgical or other procedures are not collected

^5^The date of non-study RBC transfusion, if any, during the 28-day follow-up period and 6-month extension, if applicable, must be documented

^6^Daily for inpatients when available through the end of the acute transfusion period for inpatients

^7^Performed in conjunction with every routine standard of care test for ABO Type, Rh and screen (IAT) test that is performed during the Acute Support Period

^8^If, during the acute support period or follow up assessments (Day 28), a positive DAT result is observed, participating sites will follow their routine standard practice for confirmation/characterization of DAT positive samples; this should only apply to any conversion from a negative to a positive DAT after enrollment, that is not part of an investigation of hemolysis or of a positive IAT with evidence of an amustaline/GSH RBC antibody, in which case further investigations may be appropriate after discussion with the sponsor

^9^Hematology Panel: WBC, RBC, Hb, Hct, MCV, MCH, MCHC, MPV, RDW, PLT, Neutrophil %, Monocyte %, Lymphocyte %, Basophil %, Eosinophil %

^10^Blood Chemistry Panel: BUN, Creatinine, EGFR, NA, K, GLU, Cl, CO_2_, TP, ALB, ALKP, AST (SGOT), ALT (SGPT), LDH, CPK, TBIL, DBIL

^11^Coagulation Panel: PT, INR, APTT, Fibrinogen

^12^In the outpatient setting if the subject is not seen by study staff for any other reason, surveillance calls are to be completed at least monthly (at minimum every 35 days) to collect AEs, SAEs, TRs, and UADEs starting from the initiation of the first study transfusion through the entire transfusion support period and through 28 days after the final study transfusion. If the monthly surveillance call interval coincides with a study visit, data will be collected at the study visit

**Table 2 Tab2:** Schedule of Enrollment, Interventions, and Assessments: 28-Day Plus 6-Month Extension for Sickle Cell Disease Patients Undergoing Red Cell Exchange (RCE) Patient population: Sickle Cell Disease patients on a regular, repeated RCE program receiving 3 consecutive RCE procedures. Note: Pre-allocation screening and randomization steps are the same as those in Table 1. The footnote numbering scheme in this table also maps to Table 1

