### Transfusion support periods: 28-day acute transfusion support or 28-day + 6-month extension

Subjects will receive amustaline/GSH (Test) or conventional (Control) RBCs during the transfusion support period into which they have been enrolled, or until death, whichever is first. The day of the first study transfusion will be considered study Day 1 for defining the transfusion support period. Transfusions will be administered according to local institutional policy and safety standards as ordered by the medical team.

Data on all AEs, serious AEs (SAEs), transfusion reactions (TRs) and/or Unanticipated Adverse Device Effects (UADEs) will be collected from the initiation of the first study RBC transfusion through 28 days after the last study RBC transfusion. SAEs are required to be reported by the Investigator to the Sponsor or designee immediately (i.e., no more than 24 h after learning of the event). In an inpatient setting bleeding status and safety events will be collected daily following each study RBC transfusion until discharge or death, whichever is first. In the outpatient setting surveillance calls are to be completed at least monthly (at minimum every 35 days) if the subject is not seen by study staff for any other reason. If the monthly surveillance call interval coincides with a study visit, these data may be collected as part of the study visit assessments described in Tables 1 and 2.

For pediatric patients, the volume of the intended transfusion should be recorded. Study staff will record the proportion of the transfused unit. If for any reason a unit is not fully transfused, the percentage of the bag that was transfused (i.e., 75%, 50%, 25%) and the reason the remainder of the unit was not transfused or the why the transfusion was stopped will be recorded. This proportion will be recorded for each unit of study RBCs transfused and combined with the Hb concentration and net volume of the RBC component as measured by the blood center. These variables will be used to calculate the actual Hb mass transfused.

A negative antibody screen for amustaline/GSH RBCs should be confirmed prior to transfusing a patient with study RBCs and each time a standard of care ABO Type, Rh and screen (IAT) test is performed within the 28-day acute transfusion period and the 6-month extension period, if applicable.

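### The imputed Hb content of a non-study RBC component has no term for the fraction given, so a partly transfused non-study unit enters both mITT efficacy endpoints with the wrong Hb dose

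*Protocol article*

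**What the plan says.** All references are to the Protocol article.

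- **Scope (Statistical methods).** "Non-study RBCs received during the study transfusion period will be included to calculate the total Hb content transfused for the two efficacy endpoints". This applies to the mITT set, and the endpoints meant are the adjusted Hb increment (primary) and adjusted Hb consumption (secondary).
- **Study components (Statistical methods).** The formula introduced by "The Hb content transfused (g) for a study RBC component will be calculated as" uses weight, Hb concentration and the percentage of the unit given.
- **Non-study components (Statistical methods).** "the Hb content will be imputed using the average Hb content per study RBC component from the Control group within each clinical site". No percentage term appears.
- **Recording, treatment-plan text (Transfusion support periods).** "This proportion will be recorded for each unit of study RBCs transfused". The same section adds: "For pediatric patients, the volume of the intended transfusion should be recorded". That sentence is not limited to study units.
- **Recording, schedules (Tables 1 and 2).** Both have a row that begins "Assess proportion of each RBC component transfused (e.g., 25%, 50%, 75% or 100", with no restriction to study units, and a row that begins "RBC transfusion data (study or non-study".
- **Table 1, footnote 5.** "The date of non-study RBC transfusion, if any, during the 28-day follow-up period and 6-month extension, if applicable, must be documented". The footnote mark sits on the Day 28 follow-up cell of the transfusion-data row. The transfusion-period cell is unmarked.

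**The concern.** The Hb dose is the denominator of each episode's adjusted increment and the numerator of adjusted consumption. Study units are scaled by the fraction given; under the imputation rule as written, non-study units are not. A part-unit of non-study RBCs therefore carries a dose that was not given: the increment comes out too low and consumption too high.

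Part-units are foreseeable. Enrollment starts at age 4, the protocol has recording categories below 100%, and under 18 is a planned subgroup for both endpoints. The article fixes this rule itself, and the rule sets aside a fraction that its own schedules appear to collect.

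**Working it through.** **1. The plan's own figure, for context.** Inputs from the Abstract and Sample size section: margin 15% of the Control mean, CV 50%, no true difference, two-sided alpha 0.05. In units of the Control mean, n per group = 2 × [0.50 × (1.960 + 0.842) / 0.15]², which rounds up to 175 (350 in total) by the normal approximation. The t-based calculation gives 176 (352 in total, power 0.801). The plan's 352 reproduces and is not in dispute. With 176 per group the normal approximation gives power 0.804, the baseline for step 4.

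**2. Error for one unit.** Let f be the fraction given and suppose the site mean is that of whole units. Imputed dose / true dose = 1/f. For an episode made up of that unit alone, the adjusted increment is multiplied by f.

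| f | dose counted at | increment multiplied by |
|---|---|---|
| 75% | 1.33 × true | 0.75 |
| 50% | 2 × true | 0.50 |
| 25% | 4 × true | 0.25 |

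**3. If the site mean is of Hb content actually transfused.** The rule does not say which mean is meant. With an assumed average fraction of 0.90 to 0.95 among Control units, the factor is that average divided by f: 1.20 to 1.27, 1.8 to 1.9, and 3.6 to 3.8 in the three rows. A fully given non-study unit is then understated by 5% to 10%. Individual units are still wrong, but average partial use is already in the mean.

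**4. Equal error in both arms, Hb increment.** Assume single-episode subjects, a share s affected in each arm, and f = 50%. With the true mean set to 1 and CV 0.50, the observed mean is 1 − s(1 − f) and the second moment is 1.25 × (1 − s + s f²).

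- s = 1%: mean 0.995, CV 0.503, power at 176 per group 0.799.
- s = 10%: mean 0.950, CV 0.530, power 0.756.

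The Test/Control ratio does not move; the cost is noise.

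**5. Equal error in both arms, Hb consumption.** With s now the share of units affected and f = 50%, total Hb mass is overstated by 1/(1 − 0.5s): 0.5% at s = 1% and 5.3% at s = 10%. If the overstatement is proportional in both arms, the ratio is unchanged. If instead the same grams are added to each arm, the ratio is pulled toward 1. For example, with an assumed true ratio of 1.15 and 5% of Control grams added to each arm, (1.15 + 0.05) / (1 + 0.05) = 1.143. The pull is small and in the direction that favors non-inferiority.

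**6. Unequal error, Hb increment.** A difference d between arms in the share of affected single-episode subjects moves the contrast by d × (1 − f) of the Control mean. At f = 50%, a 1% shift needs d = 0.01/0.5 = 2 percentage points; a shift equal to the whole 15% margin needs 0.15/0.5 = 30 points.

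Every s, d and f above is an assumption. The article gives no numbers of non-study, partial or pediatric transfusions.

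**The case against.** The strongest reply is that the fraction is collected. The schedules assess the proportion of each RBC component and list both study and non-study transfusion data. The treatment-plan sentence covers study units but does not exclude others, and footnote 5 sets a documentation requirement for the follow-up cell without limiting what the transfusion period collects. This stands. A reader who sees only the treatment-plan sentence and the footnote might infer that the fraction is recorded only for study units and that the data cannot be recovered. The schedules do not support that. What remains is a difference between places in the article, and an imputation rule that does not use the fraction.

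A second reply concerns size. A reader might set a twofold or fourfold unit error beside the 15% margin and infer that the conclusion is at risk. Those are unlike quantities: the margin applies to the contrast of arm means, and step 6 shows how large an imbalance would be needed. The trial is double-blind, so similar non-study use in the two arms is likely. One route to imbalance is the move to conventional RBCs after a treatment-emergent antibody. The Discussion reports four low-titer reactivities to date, arm unknown. Suppose all four were non-bleeding, all were in one arm of 176, and every one of their episodes were a quarter of a non-study unit: 4/176 × 0.75 = 1.7% of the mean. Nothing in the article suggests that this occurred. The bound does not carry over to consumption, which is analyzed only in non-bleeding extension subjects, a smaller set.

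Third, the Per Protocol analysis uses only transfusions before any non-study one, so the imputation never enters it. This also stands, although efficacy rests on the mITT set. Finally, the SAP is not shown and may already apply the fraction. In that case the article's rule should say so.

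**Conclusion.** The point holds, at minor severity. As written, the imputation gives a partly transfused non-study unit the wrong Hb dose in both mITT efficacy endpoints: about 1.33, 2 or 4 times the true dose at 75%, 50% or 25% if the site mean reflects whole units, and slightly less if it already includes partial use. The article is also not uniform on whether the fraction is recorded for non-study units.

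The effect on the trial's conclusions cannot be sized from the article. It is probably small: similar error in both arms adds noise to the increment and at most a slight pull of the consumption ratio toward 1, a large between-arm difference is unlikely under blinding, and the Per Protocol analysis is free of it. The documents do not support a claim that the non-inferiority result would be overturned.

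**What to change.** 1. In Statistical methods, define the imputed Hb content of a non-study component as the mean whole-unit Hb content of Control components at the site (weight and concentration, before the percent-transfused term) multiplied by the recorded proportion of the non-study unit transfused.
2. In the section on the transfusion support periods, align the text with Tables 1 and 2, so that the proportion is recorded for non-study as well as study units during the transfusion period.

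The cost is one sentence in each place and a matching line in the SAP, with no added visits, tests or subjects. Enrollment closed on 24 October 2025, and 28 days plus 6 months from that date runs to about late May 2026. For most subjects the second change therefore means completing the field from medical records, which are already the source data. The article states that the study remains blinded and expects the last assessments in the third quarter of 2026, so the rule can still be fixed before unblinding.
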